## Abstract

**Background:**

Despite the introduction of new insulin analogs, insulin pumps, and continuous glucose monitoring (CGM), young children with type 1 diabetes mellitus (T1D) remain vulnerable to episodes of hypoglycemia because of their unpredictable eating and activity patterns and high degree of insulin sensitivity. Caregivers and young children living with T1D learn to fear hypoglycemia because it is uncomfortable, unpredictable, and dangerous. Up to 60% of caregivers of young children with T1D report moderate to severe levels of fear of hypoglycemia, and caregiver fear of hypoglycemia relates to lower quality of life for families and suboptimal child glycemic control. Yet, until recently, there have been no studies reporting on a targeted intervention to treat caregiver fear of hypoglycemia in families of young children.

**Objective:**

The aim of this project is to conduct a randomized clinical trial of an innovative, video-based telehealth intervention to treat fear of hypoglycemia in caregivers of young children with T1D versus a relevant, age-appropriate attention control intervention.

**Methods:**

We created the Reducing Emotional Distress for Childhood Hypoglycemia in Parents (REDCHiP) intervention by merging age-appropriate T1D education and behavioral parenting strategies with cognitive behavioral therapy strategies that are effective for reducing fear and promoting adaptive coping. REDCHiP uses 10 video-based telehealth sessions that are a combination of group and individual sessions. We will recruit up to 180 families of young children with T1D to participate in this clinical trial from two pediatric diabetes clinics located in the midwestern and southern United States. Once families have been enrolled, we will randomize caregivers based on child age (age 2-3 years or 4-5 years), child sex, and family CGM use to participate in the REDCHiP or attention control intervention. Families will complete 3 assessment visits that coincide with study entry, end of treatment, and 3-month posttreatment. At each assessment visit, we will collect questionnaire data from caregivers, accelerometry data from caregivers and children, CGM data from children, and a blood sample to measure glycated hemoglobin levels from children.

**Results:**

Recruitment began in July 2019, and enrollment is ongoing. The first wave of intervention delivery began in December 2019. We anticipate completing enrollment in 2023. Final reporting of results will occur within 12 months of the primary completion date.

**Conclusions:**

If the REDCHiP intervention is efficacious, next steps will be to examine multiple implementation strategies to determine how best to disseminate the intervention to pediatric diabetes clinics around the world.

**Trial Registration:**

ClinicalTrials.gov NCT03914547; https://clinicaltrials.gov/ct2/show/NCT03914547

**International Registered Report Identifier (IRRID):**

PRR1-10.2196/17877

## Introduction

### Background

Type 1 diabetes mellitus (T1D) is a common pediatric chronic condition characterized by the loss of natural insulin production and inability to regulate blood glucose levels. Incidence rates of T1D are increasing in children aged younger than 6 years internationally [1], and data also demonstrate a 1.7% average annual increase of new cases among children aged 5 to 9 years in the United States specifically [2]. Achieving near-normal glycemic control (glycated hemoglobin [HbA_1c_] <7.5%) early in the course of T1D may reduce economic burden to the health care system, and most importantly, can reduce the risk for later T1D-related complications [3]. This goal, however, is difficult for young children with T1D and their families to achieve as only 20% of young children in the United States and 58% of young children in Europe currently meet the HbA_1c_ target of <7.5% [4]. Managing T1D is particularly challenging in young children because of their heightened insulin sensitivity, unpredictable eating behaviors, inconsistent physical activity levels, and limited communication skills [5], which lead to extreme glycemic variations and severe hypoglycemic episodes [6].

Hypoglycemia events, or low blood glucose levels, are an immediate and dangerous complication of T1D [7]. Symptoms of hypoglycemia may include headaches, dizziness, impaired consciousness, irritability, weakness, sweating, racing pulse, and, in extreme cases, seizure, coma, or death [8,9]. Prevalence rates for severe hypoglycemia in young children with T1D are 2-fold higher than older children and adolescents and 3-fold higher than adults [10]. Not surprisingly, it is common for caregivers of young children with T1D to report elevated stress and anxiety regarding the probability of their child experiencing a hypoglycemia event [11]. Unfortunately, the introduction of new technologies such as shorter and longer acting insulin analogs, insulin pumps, and continuous glucose monitors (CGMs) have not eliminated the occurrence of hypoglycemia events in young children [11-13] or reduced caregiver fear of hypoglycemia [11,14].

Up to 60% of caregivers of young children with T1D report fear of hypoglycemia, which directly affects caregiver psychological and emotional well-being [15]. Additionally, in young children with T1D, caregivers may perceive hypoglycemia as unpredictable, exacerbating their level of fear [16]. Building on past research, we developed a theoretical model for caregiver fear of hypoglycemia (Figure 1) which identifies child and caregiver variables that may underlie caregiver fear of hypoglycemia. For example, we have data suggesting that a child’s T1D history, including past experience with hypoglycemia, and a child’s sleeping behavior may relate to caregiver fear of hypoglycemia [15,17,18]. In addition, in older youth with T1D, there is evidence that child physical activity levels relate to caregiver fear of hypoglycemia [19-22].

For caregiver variables, several studies suggest that T1D-related distress, parenting stress, caregiver depressive and anxiety symptoms, and decreased caregiver sleep may exacerbate their perceptions of fear of hypoglycemia [23-27]. Our theoretical model of caregiver fear of hypoglycemia then proposes that greater caregiver fear of hypoglycemia relates to hypoglycemia avoidance behaviors, including maintaining blood glucose levels above the recommended range, treating blood glucose levels that are within the target range, and delaying or reducing insulin doses [16,28]. Our theoretical model of caregiver fear of hypoglycemia suggests that when caregivers engage in more hypoglycemia avoidance behaviors, these maladaptive coping strategies lead to chronically higher blood glucose levels, more glycemic variability, and increased risk for T1D-related complications for children [29,30]. Thus, our model suggests that caregiver fear of hypoglycemia may function as a barrier to optimal glycemic control and should be a target of behavioral interventions for families of young children with T1D.

In-person clinic visits have been a mainstay of behavioral interventions for families of youth with T1D, but this approach also presents logistical barriers (eg, travel, time, and cost). For this reason, the use of technology-based delivery methods has increased both in research and clinical settings. Access to mobile technology and the internet is ubiquitous in the United States. Current estimates suggest that 90% of American adults use the internet, 81% own smartphones, and 73% have high-speed internet access at home [31,32]. To date, most technology-based T1D interventions have focused on T1D management in adolescents and young adults versus families of young children, and the interventions have used email and text message support [33-35], websites and phone apps [36-44], and telephone counseling or video-based telehealth [45-51]. Yet these technology-based interventions suggest that it may be highly feasible and efficacious to use technology to intervene in families of youth with T1D. Moreover, using technology to intervene may be more scalable than in-person clinic delivery and enable behavioral interventions to reach a broader patient population, including families living in rural and underserved locations.

This study will fill an existing gap in the current T1D literature by developing and testing a video-based telehealth intervention to reduce caregiver fear of hypoglycemia in families of young children. Reducing Emotional Distress for Childhood Hypoglycemia in Parents (REDCHiP) uses a cognitive behavioral framework, T1D education, and behavioral parenting support to directly address caregiver fear of hypoglycemia and reduce their reliance on maladaptive coping strategies (including hypoglycemia avoidance behaviors) with the potential for downstream positive effects on young children’s T1D management and glycemic control. This paper outlines how we intend to examine the effectiveness of REDCHiP in reducing parenting stress and fear of hypoglycemia compared with an attention control intervention in a randomized clinical trial and obtain information about the intervention’s feasibility, acceptability, and impact on child glycemic control.

**Figure 1 figure1:**
[figure not shown]
Theoretical model of caregiver fear of hypoglycemia.

### Objectives

The aims of this randomized clinical trial are to (1) evaluate whether caregivers who receive the REDCHiP intervention report reductions in parenting stress and fear of hypoglycemia immediately posttreatment compared with caregivers who receive the attention control intervention; (2) evaluate whether children of caregivers who receive the REDCHiP intervention have lower HbA_1c_ and less glycemic variability posttreatment compared with children of caregivers who receive the attention control intervention; and (3) examine whether maintenance reductions in parenting stress and caregiver fear of hypoglycemia and child HbA_1c_ occur 3 months’ posttreatment for families receiving the REDCHiP intervention. Based on preliminary data, our primary hypotheses are (1) caregivers who receive REDCHiP will report reductions in parenting stress and fear of hypoglycemia compared with caregivers who receive the attention control intervention and (2) children of caregivers who receive REDCHiP will achieve more optimal glycemic control than children of caregivers who receive the attention control intervention.

## Methods

### Development of the Reducing Emotional Distress for Childhood Hypoglycemia in Parents Intervention

REDCHiP includes a cognitive behavioral framework based on the conceptualization that caregiver fear of hypoglycemia is a type of specific phobia. Individuals with specific phobias are “fearful or anxious about or avoidant of circumscribed objects or situations” and experience “fear, anxiety, or avoidance [that] is almost always immediately induced by the phobic situation, to a degree that it is persistent and out of proportion to the actual risk posed” [52]. Cognitive behavioral therapy plus systematic desensitization and exposures is a well-studied, evidence-based treatment for specific phobias in adults and demonstrates reductions in fear to a subclinical level in 90% of cases [53]. In REDCHiP, caregivers learn to recognize and alter thoughts and behaviors driven by fear of hypoglycemia and gain new behavioral parenting strategies and coping strategies to help them manage their fear. REDCHiP consists of 7 group and 3 individual sessions that are each 30 to 60 minutes in duration (Table 1).

We previously pilot-tested REDCHiP using a video-based telehealth approach. A total of 36 families completed the pilot intervention with low attrition (ie, 14%), high attendance (ie, 94%), and high caregiver-reported satisfaction [54]. Qualitatively, caregivers reported positive increases in knowledge, fear awareness, coping, and confidence and satisfaction with the support they received and the new behavioral parenting skills they learned from the REDCHiP intervention [54]. Quantitatively, caregivers experienced significant reductions in fear of hypoglycemia, parenting stress, and T1D-related distress [55]. Moreover, REDCHiP significantly reduced caregiver fear of hypoglycemia as compared against a waitlist control group, thus establishing preliminary efficacy for the REDCHiP intervention [55].

**Table 1 table1:** Overview of the Reducing Emotional Distress for Childhood Hypoglycemia in Parents intervention.

Session No.	Format	Content
1-3, 5, 7, 9-10	Group	Hypoglycemia fear is a type of phobia and behavioral parent training, cognitive behavioral framework (eg, cognitive and behavioral responses to fear) and adaptations, diabetes education (eg, managing blood glucose levels and recognizing patterns in blood glucose)
4, 6, 8	Individual	Building a fear hierarchy and guided exposure, diabetes education (eg, recognizing your child’s symptoms of high and low glucose), challenging nighttime fear, problem-solving type 1 diabetes mellitus challenges

### Attention Control Development

We used two approaches to determine the content of our attention control intervention. First, parents of young children (ages 1 to 6 years) provided input by reviewing a list of potential topics and rating each topic on a 3-point scale according to its degree of relevance to them (not relevant, somewhat relevant, or very relevant). We then selected the topics identified as very relevant by the majority of caregivers. Second, we asked 5 experts in young child development and clinical psychology to review our initial list of topics and the list of topics caregivers provided and provide recommendations for additional developmentally and age-appropriate topics. The final list of sessions includes topics relevant to young children (eg, developmental milestones, child health and safety, starting school), positive parenting strategies, and early literacy; caregivers do not learn about T1D-related topics. To complement the REDCHiP format, the attention control intervention consists of 7 group and 3 individual sessions that are each 30 to 60 minutes in duration (Table 2).

**Table 2 table2:** Overview of the attitude control intervention.

Session No.	Format	Content
1-3, 5, 7, 9-10	Group	Behavioral parent training, early childhood milestones and experiences, literacy, communication, learning through play
4, 6, 8	Individual	Early childhood safety topics (eg, injury prevention, car seat safety), creating a learning environment, establishing childhood routines and structure

### Design Considerations and Potential Challenges

We carefully designed the trial to reduce the impact of several potential challenges. First, we anticipated a challenge in recruiting an adequate sample because in very young children, T1D occurs at a prevalence of 0.29 per 1000 patients [56]. Therefore, we designed a multisite trial, which should enable us to adequately recruit our anticipated sample. Second, we anticipated barriers related to family availability and scheduling. To minimize this barrier, we designed the trial to deliver treatments via telehealth and include an option for families to complete study visits from home. Third, based on our pilot trial, we anticipated that a few eligible families (<10%) might not own a compatible device or have internet connectivity. Therefore, we have the flexibility in our trial design to loan web-enabled tablets to families. Fourth, we considered the possibility that some families might not find the intervention content or telehealth delivery favorable and will withdraw. To minimize negative trial effects due to attrition, we plan to recruit 180 families, which allows for a 20% attrition rate.

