### Randomization

This study will use a 2-arm randomized attention control design with 90 families recruited to each of the REDCHiP and attention control intervention conditions. We will stratify caregivers based on their child’s sex, child age (2 to 3 years versus 4 to 5 years) and CGM use (CGM or no CGM) and randomize to condition using blocks of eight. Recruitment and randomization will occur simultaneously across all participating sites using site-specific randomization envelopes prepared by the study biostatistician. This strategy will allow us to populate groups using caregivers from any site, thereby improving our recruitment efficiency and minimizing possible clinic effects.

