Of note, the study protocol will enable families to complete study visits either in their home, at the diabetes clinic, or at another location (eg, library). Additionally, our protocol includes strategies to retain families in the study in the rare event that they move away (eg, telehealth, online surveys, mail-in HbA_1c_ kits) or recruit families who self-refer based on word of mouth or ClinicalTrials.gov. All participating caregivers and children will receive compensation for study visits 1 through 3. As needed, the study will use prepaid postage boxes for families to return study-related devices (eg, accelerometers and CGM sensors) to further reduce the burden on participating families.

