### Data Analysis Plan

We will measure parenting stress and caregiver fear of hypoglycemia using the Pediatric Inventory for Parents [64] and the Hypoglycemia Fear Survey–Parents of Young Children [15,26], respectively. We will use child HbA_1c_ levels and percentage of time in range (eg, 70 to 180 mg/dL) to examine child glycemic control and glycemic variability, respectively. To test for treatment outcomes, we will model study visit 2 scores as a function of visit 1 scores, condition (REDCHiP versus attention control intervention), and selected covariates (eg, race/ethnicity, pump use) in mixed models that include a random intercept to account for clustering of participants within group cohorts. We will accommodate nonnormal outcome variables with log transformation, modeling with an appropriate generalized mixed model or nonparametric test. We will test the effect of condition based on whether the 95% confidence interval for the condition coefficient includes zero (equivalent to a 2-sided test at α=.05). To determine long-term treatment effects, we will test for sustained improvement on outcome variables by modeling scores at study visit 3 as a function of visit 1 scores and condition (REDCHiP versus attention control intervention). To control the overall rate of type I errors, we will conduct these analyses only for variables with a statistically significant condition effect in our primary analysis of treatment outcomes.

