### Power Analysis

We anticipate recruiting 180 families, allowing for a 20% attrition rate and resulting in a final goal of completing the trial with at least 144 families. We assessed power using a simulation study; each simulated dataset contained 40 clusters (20 REDCHiP, 20 attention control intervention) of 4 to 5 participants each. We simulated posttreatment scores using the following model: Y_ij_ = rX_ij_ + u_i_ + ES×Condition_i_ + ε_ij_, where Y_ij_ is the posttreatment score for the *j*th participant in the *i*th cluster, r is the within-cluster correlation between baseline and posttreatment scores (set to .72 based on pilot data), X_ij_ is the *ij*th participant’s baseline score, u_i_ is the normally distributed random intercept for the *i*th cluster, ES is the standardized effect size (set to 0.6 standard deviations based on pilot data), Condition is an indicator (1 for REDCHiP, 0 for attention control intervention), and ε is a normally distributed error term. The variances of u_i_ and ε_ij_ were set to yield a within-condition intraclass correlation coefficient of .10. We fit a mixed model with a random cluster intercept and baseline score and condition as predictors to each of 1000 simulated data sets. To compute estimated power we took the average number of data sets for which the condition was statistically significant in a 2-sided test at α=.05. Based on the indicated parameter values and sample size, estimated power was 83%. For 40 groups averaging 3.6 families each, estimated power was 90%. Recognizing this trial will include a control group, which could attenuate our REDCHiP effect, if we conservatively reduce the standardized effect size to 0.4 standard deviations, estimated power is 85%.

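### Over-recruiting protects precision, not comparability, and the separate visit 3 model leaves unused the visit 2 scores of families lost before visit 3

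*Protocol article*

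**What the plan says.** Under Design Considerations and Potential Challenges, the protocol article raises the possibility that "some families might not find the intervention content or telehealth delivery favorable and will withdraw". The response given there is: "To minimize negative trial effects due to attrition, we plan to recruit 180 families, which allows for a 20% attrition rate". The Power Analysis carries the same figures, "resulting in a final goal of completing the trial with at least 144 families", and Randomization describes a "2-arm randomized attention control design with 90 families recruited to each of the REDCHiP and attention control intervention conditions".

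The Data Analysis Plan states one model per visit. The end-of-treatment comparison is specified as "we will model study visit 2 scores as a function of visit 1 scores, condition (REDCHiP versus attention control intervention), and selected covariates", with a random intercept for group cohort. For maintenance, the plan is "modeling scores at study visit 3 as a function of visit 1 scores and condition (REDCHiP versus attention control intervention"), run only for outcomes with a significant condition effect at visit 2.

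On retention, Study Visit Procedures says "our protocol includes strategies to retain families in the study in the rare event that they move away", and names online surveys and mail-in HbA1c kits among the means. The same section lets every family choose the visit location, compensates all three visits, and describes visits 2 and 3 as completed by all families.

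**The concern.** Adding families to the intake replaces numbers. It does not replace the particular families who leave. The arms differ in content: REDCHiP includes a fear hierarchy and guided exposure, while the control sessions teach nothing about T1D. Leaving because of content may therefore have different causes in each arm and remove different kinds of family.

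The stated visit 3 model adds to this. A caregiver who attends visit 2 and then leaves has supplied the best available predictor of the missing visit 3 score, yet the model conditions on visit 1 and arm alone. If leaving is related to how visit 2 turned out, and differently by arm, the families left at visit 3 are no longer comparable given visit 1. At stake is aim 3, the claim that reductions in stress, fear and HbA1c are maintained at 3 months.

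**Working it through.** **1. The plan's own figures.** 144/(1 − 0.20) = 180, and 180 × 0.80 = 144. The Power Analysis is consistent with this: 40 groups × 3.6 families = 144, and 40 × 4.5 = 180. The inflation is correct. The shifts computed below depend on who is lost, not on how many are recruited.

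**2. Which scores each model uses, as worded.**

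| Family has | Visit 2 model | Visit 3 model |
|---|---|---|
| visits 1, 2, 3 | used | used |
| visits 1, 2 | used | not used; visit 2 score ignored |
| visits 1, 3 | not used | used |
| visit 1 only | not used | not used |

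**3. Size of the visit 3 shift.** From the Power Analysis: r = .72 and a reduced effect of 0.40 SD. The residual SD given baseline is √(1 − 0.72²) = √0.4816 = 0.694.

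Assumed, because the documents do not give them:
- correlation ρ = 0.6 between visit 2 and visit 3 residuals;
- correlation s = 0.5 between the tendency to leave and a poor visit 2 residual;
- loss d after visit 2;
- the same true effect at both visits, with the cohort intercept left out for simplicity.

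Selection in one arm shifts that arm's mean visit 3 residual, among families retained, by

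ρ × s × 0.694 × φ(z)/(1 − d), where z is the (1 − d) normal quantile.

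- d = 0.15: 0.6 × 0.5 × 0.694 × 0.2332/0.85 = 0.057
- d = 0.16: 0.6 × 0.5 × 0.694 × 0.2433/0.84 = 0.060
- d = 0.17: 0.6 × 0.5 × 0.694 × 0.2531/0.83 = 0.063

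Results at visit 3 for a true 0.40 SD:

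| Loss after visit 2 depends on the visit 2 result | Stated visit 3 model | Joint visit 2 and 3 likelihood |
|---|---|---|
| in REDCHiP only (15-17%) | about 0.46 | 0.40 |
| in control only (15-17%) | about 0.34 | 0.40 |
| alike in both arms, equal rates | 0.40 | 0.40 |
| in both arms, 30% REDCHiP and 10% control | 0.46 | 0.40 |

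Simulation agrees with the formula. A shift of 0.06 is 0.06/0.40 = 15% of the effect. It is proportional to ρ and to s, so halving either halves it. With 10% loss it is 0.6 × 0.5 × 0.694 × 0.1755/0.90 = 0.041, giving about 0.36 to 0.44.

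**4. What the joint model cannot repair.** If loss occurs before visit 2 and is tied to the unseen outcome (s from 0.2 to 0.5), the visit 2 estimate shifts by +0.02 to +0.05 SD at 25% REDCHiP and 15% control loss, and by +0.04 to +0.11 at 30% and 10%. With the rates reversed the shifts are the same size and negative. At 20% in each arm the shift is zero. A family with no score after baseline adds no outcome information to either form of analysis.

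**The case against.** The strongest reply is that a condensed article need not declare an analysis set or a missing-data method. This one neither states nor rules out intention-to-treat, imputation or sensitivity analyses, and the full protocol or SAP may supply them. That stands, and their absence is not part of this point. The point rests on the visit 3 model that the article does state.

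A reader might infer that over-recruitment is the only answer to attrition. It is not: the article also lists home visits, tablet loans, compensation, mail-in kits, online questionnaires and technology support. Nor does it make visits 2 and 3 conditional on attending sessions, so following up families who stop is largely compatible with the text. What is missing is a sentence that separates stopping sessions from leaving the study.

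A reader might also infer that the REDCHiP effect is overstated. If 20% of REDCHiP families stopped, gained nothing and went unmeasured, a completer effect of 0.60 would stand for 0.60 × 0.80 = 0.48, an overstatement of 25%. The documents do not support that as a finding. The 20% is an all-cause allowance, the pilot had 14% attrition with 94% attendance, and no rate by arm is given. Both arms have ten telehealth sessions in matched format, and control families may leave because their sessions omit T1D. The joint model would not correct that scenario in any case.

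Finally, visit 3 is a gated secondary analysis, and baseline-adjusted analysis at one visit is standard. That limits the weight of the point but does not remove it.

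**Conclusion.** The point holds in limited form. Recruiting 180 to keep 144 is correct for precision and does nothing about bias from withdrawal related to the intervention. The stated visit 3 model discards visit 2 scores that bear on the missing visit 3 scores. Its maintenance estimate could fall anywhere from about 0.34 to 0.46 SD for a true 0.40, if 15-17% of families are lost after visit 2 and that loss depends on the visit 2 result in one arm only. It is unbiased if loss acts alike in both arms.

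The range rests on the assumed correlations (0.6 between visits, 0.5 between leaving and result). It also rests on a loss after visit 2 that would use most of the 20% allowed for the whole trial, so it lies towards the upper end of what the plan foresees. The direction is unknown. Neither an inflated treatment effect nor a declared completers-only analysis can be read from the article.

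**What to change.** **Data Analysis Plan.** Estimate the visit 2 and visit 3 contrasts from one likelihood-based repeated-measures mixed model. Include the visit 1 score, arm-by-visit terms, the cohort random intercept and a within-family covariance across visits, with every family in its assigned arm. Keep the present rule that visit 3 is tested only where visit 2 is significant.

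**Design Considerations and Study Visit Procedures.** State that families who stop sessions are distinct from families who leave the study, and that the former are still asked for the online surveys and mail-in HbA1c sample at visits 2 and 3. This is needed alongside the model, which cannot recover families with no score after baseline.

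**Cost.** Slightly more analysis work, two or three sentences of text, and a few extra mailings and reminders. The remote surveys and kits already exist.
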